| Statistical Considerations:            | 
The primary analysis is an intention-to-treat (ITT) analysis, i.e. all patients will be analysed in the group they were originally allocated to.
 
Secondary analyses will be performed per protocol (PP), i.e. only patients that in fact received the study treatment according to the randomization will be analysed.
 
Patient characteristics will be presented as frequency and percentage for binary variables, mean and standard deviation for continuous, normally distributed variables, and median and interquartile range for continuous, non-normally distributed variables.
 
The primary and all secondary binary outcomes will be evaluated descriptively in each group presenting proportions with 95% Wilson confidence intervals.
 
Additionally, we will compare the primary and all secondary binary outcomes using a Cochran-Mantel-Haenszel-test stratified for the stratification factors used in the randomization. These tests will be exploratory, not confirmatory.
 
Pharmacokinetic and pharmacodynamic parameters will be presented in each treatment group as median with interquartile range and mean with 95% confidence interval.
 |
| GCP Statement:                         | This study will be conducted in compliance with the protocol, the current version of the Declaration of Helsinki, the ICH-GCP as well as all national legal and regulatory requirements.                                                                                                                                                                                                                                                                                                                                                                                                                                                                                                                                                                                                                                                                                                                                                                                                                                                                                                                                                                                                             |

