| Objective(s):                | 
Primary objectives
 
To assess the safety and feasibility of VTE prophylaxis with 10 mg rivaroxaban QD for 7 and 28 days, respectively
 
Secondary objectives
 
 
- To compare VTE prophylaxis with 10 mg rivaroxaban QD for 7 and 28 days, respectively, regarding thromboembolic events.
 
- To assess the postoperative rates of asymptomatic DVT, symptomatic DVT, symptomatic PE, bleeding events, and investigator-reported adverse events (morbidity and mortality).
 
- To assess the pharmacokinetic effect of 10 mg rivaroxaban after repeated administration in bariatric surgery (subgroup of patients)
 
- To assess the pharmacodynamic effect of 10 mg rivaroxaban after bariatric surgery (subgroup of patients)
 
                                                                                                                                                                                                              |

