### **3.7 Risks / Benefits**

Since rivaroxaban is already approved in different indications, there is no general concern regarding its risk profile. The major risk is associated with bleeding. On the other side, ischemic events can be prevented with successful thromboembolic prophylaxis.

Bariatric surgery is performed according to clinical routine. Patients receive the first postoperative dose of rivaroxaban (10 mg) on the first postoperative day. Data of our previous single dose PK/PD study have shown PK/PD effects comparable to non-bariatric postsurgical patients without evidence of a bleeding or a thromboembolic adverse event.

Currently, there is no common recommendation available regarding the duration of VTE prophylaxis in post-bariatric patients. The benefit of this trial will be the generation of new safety and efficacy data regarding the duration of VTE prophylaxis in this specific patient population.

Prophylaxis with rivaroxaban had a significantly higher efficacy in VTE prophylaxis as compared with enoxaparin after hip and knee replacement surgery as was shown in the large RECORD clinical trial programme with similar rates of bleeding [29-32].

With this clinical phase 2 trial that is based on our previous phase 1 PK/PD trial [24], safety and feasibility of an anticoagulation with rivaroxaban will be investigated in bariatric patients. Since to date there is no phase 2 data available for bariatric patients, this trial will be the next step needed to finally introduce a prophylactic anticoagulation with rivaroxaban in bariatric patients.

In case of confirmed safety and efficacy, oral anticoagulation with rivaroxaban will be beneficial for bariatric patients due to the facilitated application in form of tablets compared to daily subcutaneous injections of low-molecular weight heparins (LMWH) after surgery.

Based on the data of our phase 1 PK/PD trial [24] as well as of the available evidence from multiple trials in similar orthopaedic indications [29-32], the risk of the anticoagulation with the investigational product is similar to the standard of care application of LMWH.

With the methodology used in this study (details regarding the sample size calculation see at 11.2), new generalizable information will be generated for both study arms.

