The most common adverse reactions with Xarelto® are bleeding complications. To minimize the risk for bleeding event, patients with an a priori higher risk for bleeding are excluded from this clinical trial.

The primary safety endpoint will be major bleeding. All adverse events will be collected and processed according to international guidelines and national legislation. Conduct of this clinical trial will be monitored by an independent third party.

Embryo-foetal toxicity (post-implantation loss, retarded/progressed ossification, hepatic multiple light coloured spots) and an increased incidence of common malformations as well as placental changes were observed at clinically relevant plasma concentrations. Therefore, use of a double barrier contraception method during the study is mandatory to minimize the risk for embryo-foetal toxicity.

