### 4.2 Primary Objective

To assess the safety and feasibility of VTE prophylaxis with 10 mg rivaroxaban QD for 7 and 28 days, respectively.

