### 4.3 Secondary Objectives

- To compare VTE prophylaxis with 10 mg rivaroxaban QD for 7 and 28 days, respectively, regarding thromboembolic events.
- To assess the postoperative rates of asymptomatic DVT, symptomatic DVT, symptomatic PE, bleeding events, and investigator-reported adverse events (morbidity and mortality).
- To assess the pharmacokinetic effect of 10 mg rivaroxaban after repeated administration in bariatric surgery (subgroup of 32 patients)
- To assess the pharmacodynamic effects of 10 mg rivaroxaban after bariatric surgery (subgroup of 32 patients)

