#### Primary safety variables

Major bleeding within 28 days after bariatric surgery as defined by the ISTH [37].

Major bleeding is defined as a bleeding event that meets at least one of the following criteria:

- fatal bleeding
- critical bleeding (intracranial, intraocular, intraspinal, pericardial, retroperitoneal, in a nonoperated joint, or intramuscular with compartment syndrome)
- clinically overt bleeding (at surgical or extrasurgical site) associated with a decrease in the haemoglobin level of more than 2 g/dL (20 g/L; 1.24 mmol/L) compared with the prerandomisation level
- clinically overt bleeding (at surgical or extrasurgical site) leading to transfusion of two or more units of whole blood or packed cells
- bleeding located at the surgical site and leading to re-operation or to any unusual medical intervention or procedure for relief (e.g. draining or puncture of a haematoma at the surgical site, transfer to an ICU or emergency room)

The occurrence and classification of all components of the composite endpoint and safety outcomes will be centrally adjudicated by an independent and blinded committee of experts.

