#### 11.4.4 Secondary Analyses

Secondary analyses will be performed per protocol (PP), i.e. only patients that in fact received the study treatment according to the randomization will be analysed. Secondary analyses will be reported for the FAS, the SGAS and the RYAS.

Following secondary outcomes will be analysed:

- Symptomatic VTE within 28 days after bariatric surgery
- Asymptomatic VTE within 28 days after bariatric surgery
- All-cause mortality within 28 days after bariatric surgery
- Postoperative morbidity (Dindo-Clavien classification) within 28 days after bariatric surgery
- VTE-related death within 28 days postoperatively
- PK/PD (subset of 32 patients)

The secondary binary outcomes will be evaluated descriptively in each group presenting proportions with 95% Wilson confidence intervals. Additionally, we will compare the secondary binary outcomes using a Cochran-Mantel-Haenszel-test stratified for the stratification factors used in the randomization. These tests will be exploratory, not confirmatory.

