#### **11.4.6 Safety analysis**

All adverse events and serious adverse events will be assessed regarding relatedness to study drug and presented in tabular form indicating absolute numbers of events and percentages. The safety analysis will be performed on the FAS.

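### The planned comparisons of 7 with 28 days of rivaroxaban cover VTE but not major bleeding, the primary safety endpoint

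*Protocol*

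**What the plan says.** **Objectives.** The primary objective (4.2) is "To assess the safety and feasibility of VTE prophylaxis with 10 mg rivaroxaban QD for 7 and 28 days, respectively". Of the secondary objectives in the synopsis and 4.3, only one is worded as a comparison of the arms: "To compare VTE prophylaxis with 10 mg rivaroxaban QD for 7 and 28 days, respectively, regarding thromboembolic events". Bleeding events appear in the next objective, where rates are to be assessed rather than compared.

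**Between-arm analyses.** Section 11.4.3 plans an exploratory stratified CMH test for the primary outcome, VTE. Section 11.4.4 adds: "Additionally, we will compare the secondary binary outcomes using a Cochran-Mantel-Haenszel-test stratified for the stratification factors used in the randomization". The outcomes it lists are symptomatic VTE, asymptomatic VTE, all-cause mortality, Dindo-Clavien morbidity, VTE-related death and PK/PD. The statistical considerations in the synopsis draw the same boundary: the primary outcome and all secondary binary outcomes.

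**Bleeding.** Section 3.7 states: "The primary safety endpoint will be major bleeding", and 5.4 repeats this. Section 9.3.1 defines the variable as "Major bleeding within 28 days after bariatric surgery as defined by the ISTH" and sends it to blinded central adjudication. Section 11.4.6 says that adverse events will be "presented in tabular form indicating absolute numbers of events and percentages", on the FAS. Section 11.2 also has a general sentence under which every outcome is described per group with a 95% confidence interval.

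**Purpose.** Section 3.7 gives the benefit of the trial as the "generation of new safety and efficacy data regarding the duration of VTE prophylaxis".

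**The concern.** The arms receive the same 10 mg dose and differ in duration only, by 28 - 7 = 21 days. Longer treatment is expected to lower VTE. Its main expected cost is bleeding, which 3.7 names as the major risk. A report that follows the protocol would contain a between-arm contrast for the first and none for the second.

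This is not a detail left to a statistical analysis plan. The protocol itself names the outcomes to be compared, and its primary safety endpoint is not among them. What is at stake is how the trial informs the duration question and the phase III design mentioned in 3.1: one side of the trade-off would come with a comparison and the other would not.

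**Working it through.** **1. The protocol's own figures.** Section 11.2 assumes 28-day VTE of 0.5% (extended) and 5% (short) with 130 per arm, and gives expected 95% Wilson intervals of 0.1-3.7% and 2.4-10.1%. Averaging the Wilson limits over the Bin(130, p) distribution gives 0.12-3.72% and 2.44-10.14%. The figures reproduce. The expected VTE gain is 5.0 - 0.5 = 4.5 points.

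**2. Which outcomes have a planned between-arm contrast.**

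| Outcome | Status in the protocol | Between-arm contrast |
|---|---|---|
| VTE | primary outcome | CMH, 11.4.3 |
| Symptomatic VTE, asymptomatic VTE, VTE-related death | secondary | CMH, 11.4.4 |
| All-cause mortality | secondary | CMH, 11.4.4 |
| Dindo-Clavien morbidity | secondary, graded, no binary cut stated | listed in 11.4.4; CMH only if made binary |
| Major bleeding | primary safety endpoint | none |
| Clinically relevant non-major bleeding | additional safety variable | none |

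**3. What the missing contrast would look like.** The protocol gives no bleeding rate, so everything here is an assumption. Take 1/130 major bleeds in the 7-day arm and 4/130 in the 28-day arm.

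- Proportions and Wilson limits: p1 = 1/130 = 0.77% (0.14 to 4.23); p2 = 4/130 = 3.08% (1.20 to 7.64).
- Difference: d = p2 - p1 = 2.31 points.
- Newcombe lower limit: d - √[(p2 - l2)² + (u1 - p1)²] = 2.31 - √[(3.08 - 1.20)² + (4.23 - 0.77)²] = 2.31 - 3.94 = -1.6.
- Newcombe upper limit: d + √[(u2 - p2)² + (p1 - l1)²] = 2.31 + √[(7.64 - 3.08)² + (0.77 - 0.14)²] = 2.31 + 4.60 = +6.9.

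The same method at other assumed rates, with 130 per arm:

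| 7-day arm | 28-day arm | Difference (95% interval), points | Approximate power |
|---|---|---|---|
| 1% | 1% | 0.0 (-3.7 to 3.7) | - |
| 1% | 2% | +1.0 (-2.9 to 5.2) | 10% |
| 1% | 3% | +2.0 (-2.0 to 6.6) | 21% |
| 2% | 4% | +2.0 (-2.7 to 7.1) | 16% |

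**4. The VTE contrast on the same footing.** At the protocol's rates the Newcombe interval for the VTE gain is 4.5 points (0.3 to 9.7). Both contrasts are wide. The like-for-like comparison is interval with interval: an upper limit for bleeding should not be set against the point estimate for VTE.

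**The case against.** The best case for leaving the plan alone has four parts.

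- **Bleeding is not neglected.** Safety of both durations is the primary objective, 4.4 adds a bleeding-related safety objective, and adjudication is blinded. On the wording of 11.2 each arm gets an estimate with a 95% interval: in the example, 0.8% (0.1-4.2) and 3.1% (1.2-7.6). A reader could work out the difference from the counts. This stands, and it means that the gap is confined to the between-arm statement.
- **The comparisons are not confined to VTE.** All-cause mortality and Dindo-Clavien morbidity are also listed, and the long arm could do worse on either. This stands too, but neither isolates bleeding, and the morbidity scale has no binary cut to which CMH could be applied.
- **All contrasts are exploratory.** Sections 11.1 and 11.2 rule out formal testing, and no decision rule rests on VTE. This lowers the stakes. It does not explain why the exploratory contrasts include VTE and omit the primary safety endpoint.
- **A bleeding contrast would be imprecise.** That is true, with about 10-21% power in the scenarios with a difference. It is a reason to show the interval, since a per-arm table invites the reader to take a small difference in counts as no difference.

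A reader might go further and infer that the 28-day arm can only look better, or that the duration question is settled for it by construction. The documents do not support this. At the protocol's rates the 28-day arm shows fewer VTEs with probability 98.8%. If the true rate were 5% in both arms it would look worse in 44% of trials, and at 2% (short) versus 1% (extended) in 17%.

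**Conclusion.** The point holds as an asymmetry in the named comparisons. The comparison objective and the CMH lists cover the expected benefit of longer treatment and omit major bleeding, which is described per arm only. The omission can be read from the protocol's text and needs no assumption. Its size cannot be derived from the documents, because they give no bleeding rate. At assumed rates of 1-4% the missing interval would reach roughly 4 points on either side of the difference, somewhat more on the upper side. The finding does not show that the conclusion on duration is predetermined, that bleeding goes unreported, or that the sample size must change. It is worth correcting because the trial presents itself as a source of both safety and efficacy data on duration.

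**What to change.** 1. In the synopsis and 4.3, extend the comparison objective to thromboembolic events and adjudicated major bleeding.
2. In 11.4, report the between-arm risk difference with a 95% interval (for example Newcombe) for major bleeding, and likewise for clinically relevant non-major bleeding, on the FAS. Place it beside the same contrast for VTE and label all of it exploratory.

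The cost is a few lines of text and a few table rows. Major bleeding is already collected and adjudicated over 28 days, so no new data, visits or patients are needed. The drawback is an imprecise interval, which should be presented as such.

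A descriptive outcome of VTE or major bleeding, with its components beside it, is optional. Unweighted, it counts an ultrasound-detected calf thrombosis and a major bleed as equal, so it should not be a condition of the fix.

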## STUDY SUMMARY IN LOCAL LANGUAGE

Bei dieser klinischen Studie, die in mehreren Zentren für Übergewichtschirurgie durchgeführt wird, wird die Wirkung des Medikamentes Xarelto (Rivaroxaban) 10 mg zur Verhinderung (Prophylaxe) von Thrombosen und Lungenembolien im Anschluss an die Übergewichtschirurgie untersucht. Patientinnen und Patienten erhalten im Anschluss an die Operation entweder während 7 oder während 28 Tagen das gerinnungshemmende Medikament Xarelto. Nach 28 Tagen erfolgt eine Kontrolle der Beinvenen mittels Ultraschall, um auch Thrombosen festzustellen, die nicht zu Beschwerden geführt haben. Bei einem Teil der Studienpatienten werden im Anschluss an die letzte Einnahme des Studienmedikaments über die Dauer von 24 Stunden zusätzliche Untersuchungen zur Konzentration und zur Wirkung von Xarelto durchgeführt.

## ABBREVIATIONS

|       |                                                                                                  |
|-------|--------------------------------------------------------------------------------------------------|
| AE    | Adverse Event                                                                                    |
| aPTT  | Activated Partial Thromboplastin Time                                                            |
| ASA   | American Society of Anesthesiologists physical status classification system                      |
| AUC   | Area Under the Curve                                                                             |
| BMI   | Body Mass Index                                                                                  |
| CA    | Competent Authority (e.g. Swissmedic)                                                            |
| CEC   | Competent Ethics Committee                                                                       |
| Cmax  | Maximum Plasma Concentration                                                                     |
| Cmin  | Minimal Plasma Concentration                                                                     |
| CRF   | Case Report Form                                                                                 |
| ClinO | Ordinance on Clinical Trials in Human Research (in German: KlinV, in French: OClin)              |
| CTCAE | Common terminology criteria for adverse events                                                   |
| DSUR  | Development safety update report                                                                 |
| DVT   | Deep vein thrombosis                                                                             |
| eCRF  | Electronic Case Report Form                                                                      |
| F1+2  | Thrombin fragments                                                                               |
| FAS   | Full Analysis Set                                                                                |
| GCP   | Good Clinical Practice                                                                           |
| GFR   | Glomerular Filtration Rate (Creatinin clearance)                                                 |
| IB    | Investigator's Brochure                                                                          |
| HFG   | Humanforschungsgesetz (Law on human research, LHR)                                               |
| HMG   | Heilmittelgesetz                                                                                 |
| HRA   | Federal Act on Research involving Human Beings                                                   |
| IMP   | Investigational Medicinal Product                                                                |
| IIT   | Investigator-initiated Trial                                                                     |
| ITT   | Intention to treat                                                                               |
| KlinV | Verordnung über klinische Versuche in der Humanforschung
(in English: ClinO, in French OClin) |
| LMWE  | Low Molecular Weight Heparin                                                                     |
| PE    | Pulmonary Embolism                                                                               |
| PI    | Principal Investigator                                                                           |

|       |                                               |
|-------|-----------------------------------------------|
| POD   | Postoperative Day                             |
| PP    | Per Protocol                                  |
| PT    | Prothrombin time                              |
| RYGB  | Roux-en-Y gastric bypass                      |
| RYAS  | Roux-en-Y gastric bypass Analysis Set         |
| SDV   | Source Data Verification                      |
| SG    | Sleeve Gastrectomy                            |
| SGAS  | Sleeve Gastrectomy Analysis Set               |
| SOP   | Standard Operating Procedure                  |
| SPC   | Summary of product characteristics            |
| SUSAR | Suspected Unexpected Serious Adverse Reaction |
| TAT   | Thrombin-Antithrombin-Complexes               |
| Tmax  | Time of Maximum Plasma Concentration          |
| TMF   | Trial Master File                             |
| VTE   | Venous Thromboembolism                        |

## STUDY SCHEDULE

| Study period                                                                         | Screening  | Surgery           | Postoperative |    |    |     |     |      |      |       |      |       |                                               |     |     |     |     |     |       |      |     |     |                |
|--------------------------------------------------------------------------------------|------------|-------------------|---------------|----|----|-----|-----|------|------|-------|------|-------|-----------------------------------------------|-----|-----|-----|-----|-----|-------|------|-----|-----|----------------|
| Study visit                                                                          | V0         |                   | V1            | V2 | V3 |     | V4  |      | V5   |       | V6   |       | V7                                            |     |     |     |     |     | V8    | V9   |     |     |                |
| Study day                                                                            | -30 bis -1 | 0                 | 1             | 2  | 3  | 4-7 | 8±2 | 9-14 | 15±2 | 16-20 | 21±2 | 22-27 | 28±2                                          |     |     |     |     |     | V7+1  | V7+7 |     |     |                |
| Hosp day                                                                             |            | 1                 | 2             | 3  | 4  |     |     |      |      |       |      |       |                                               |     |     |     |     |     |       |      |     |     |                |
| Time (24 h clock)                                                                    |            | 8 18 + | 8             | 8  | 8  | 8   | 8   |      | 8    |       | 8    |       | 7                                             | 8   | 9   | 10  | 11  | 12  | 14    | 16   | 20  | 8   |                |
| Relative time points for PK/PD (32 patients, 16 RYGB, 16 SG, Insepsital Bern only)** |            |                   |               |    |    |     |     |      |      |       |      |       | T -1h T 0 T 1h T 2h T 3h T 4h T 6h T 8h T 12h |     |     |     |     |     | T 24h |      |     |     |                |
| Informed consent                                                                     | x          |                   |               |    |    |     |     |      |      |       |      |       |                                               |     |     |     |     |     |       |      |     |     |                |
| Medical history                                                                      | X          |                   |               |    |    |     |     |      |      |       |      |       |                                               |     |     |     |     |     |       |      |     |     |                |
| Concomitant medication                                                               | x          |                   |               |    |    |     |     |      |      |       |      |       |                                               |     |     |     |     |     |       |      |     |     |                |
| Demographics                                                                         | x          |                   |               |    |    |     |     |      |      |       |      |       |                                               |     |     |     |     |     |       |      |     |     |                |
| Physical exam incl. weight and height                                                | x          |                   |               |    |    |     |     |      |      |       |      |       |                                               |     |     |     |     |     |       |      |     |     |                |
| Inclusion/Exclusion-criteria                                                         | x          |                   |               |    |    |     |     |      |      |       |      |       |                                               |     |     |     |     |     |       |      |     |     |                |
| Coagulation/hemostasis parameters (INR, Platelets)                                   | x          |                   |               |    |    |     |     |      |      |       |      |       |                                               |     |     |     |     |     |       |      |     |     |                |
| Liver and kidney function                                                            | x          |                   |               |    |    |     |     |      |      |       |      |       |                                               |     |     |     |     |     |       |      |     |     |                |
| Beta-HCG                                                                             | x          |                   |               |    |    |     |     |      |      |       |      |       |                                               |     |     |     |     |     |       |      |     |     |                |
| Bariatric Surgery                                                                    |            | x ++   |               |    |    |     |     |      |      |       |      |       |                                               |     |     |     |     |     |       |      |     |     |                |
| Study inclusion                                                                      |            |                   | x             |    |    |     |     |      |      |       |      |       |                                               |     |     |     |     |     |       |      |     |     |                |
| Randomization                                                                        |            |                   | x             |    |    |     |     |      |      |       |      |       |                                               |     |     |     |     |     |       |      |     |     |                |
| Discharge (earliest point of time)                                                   |            |                   |               | x  |    |     |     |      |      |       |      |       |                                               |     |     |     |     |     |       |      |     |     |                |
| Study arms                                                                           |            |                   |               |    |    |     |     |      |      |       |      |       |                                               |     |     |     |     |     |       |      |     |     |                |
| A: Rivaroxaban short arm                                                             |            |                   |               |    |    |     |     |      |      |       |      |       |                                               |     |     |     |     |     |       |      |     |     |                |
| LMWH in prophylactic dose (e.g. Clexane, Fraxiparine)                                |            | x                 |               |    |    |     |     |      |      |       |      |       |                                               |     |     |     |     |     |       |      |     |     |                |
| Rivaroxaban 10 mg p.o. QD                                                            |            |                   | x             | x  | x  | x   |     |      |      |       |      |       |                                               |     |     |     |     |     |       |      |     |     |                |
| B: Rivaroxaban long arm                                                              |            |                   |               |    |    |     |     |      |      |       |      |       |                                               |     |     |     |     |     |       |      |     |     |                |
| LMWH in prophylactic dose (e.g. Clexane, Fraxiparine)                                |            | x                 |               |    |    |     |     |      |      |       |      |       |                                               |     |     |     |     |     |       |      |     |     |                |
| Rivaroxaban 10 mg p.o. QD                                                            |            |                   | x             | x  | x  | x   | x   | x    | x    | x     | x    | x     |                                               |     |     |     |     |     |       |      |     |     |                |
| Duplex sonography                                                                    |            |                   |               |    |    |     |     |      |      |       |      |       | x                                             |     |     |     |     |     |       |      |     |     |                |
| PK/PD substudy                                                                       |            |                   |               |    |    |     |     |      |      |       |      |       |                                               |     |     |     |     |     |       |      |     |     |                |
| Anti Xa activity**                                                                   |            |                   |               |    |    |     | x   |      | x    |       | x    |       | x                                             | x   | x   | x   | x   | x   | x     | x    | x   | x   |                |
| Rivaroxaban Concentration**                                                          |            |                   |               |    |    |     | x   |      | x    |       | x    |       | x                                             | x   | x   | x   | x   | x   | x     | x    | x   | x   |                |
| Thrombin-Antithrombin-Complex (TAT)**                                                |            |                   |               |    |    |     |     |      |      |       |      |       | x                                             | x   | x   | x   | x   | x   | x     | x    | x   | x   |                |
| Prothrombin-Fragments (F1 + F2)**                                                    |            |                   |               |    |    |     |     |      |      |       |      |       | x                                             | x   | x   | x   | x   | x   | x     | x    | x   | x   |                |
| Thrombin Generation**                                                                |            |                   |               |    |    |     |     |      |      |       |      |       | x                                             | x   | x   | x   | x   | x   | x     | x    | x   | x   |                |
| D-Dimers                                                                             | x**        |                   | x**           |    |    |     |     |      | x**  |       | x**  |       | x                                             | x** | x** | x** | x** | x** | x**   | x**  | x** | x** |                |
| AEs/SAEs                                                                             |            | x                 | x             | x  | x  | x   |     | x    |      | x     |      | x     |                                               | x   | x   | x   | x   | x   | x     | x    | x   | x   | x + |

\*1st dose 6–8 h after wound closure or after adequate haemostasis has been achieved, subsequent doses at 8 am

\*\* Study independent bariatric surgery

\* Telephone call

\*\* Analysis PK/PD 32 patients

